### Interventions

#### Usual care

Women will receive the same care as is now provided in the three participating hospitals. Women are typically admitted on the day of surgery and are discharged 2 to 7 days after surgery. While in hospital, they are seen by a physiotherapist who reviews gentle shoulder exercises which are outlined in a pamphlet. The active assisted shoulder exercises are for shoulder protraction, elevation and abduction. In addition, women are seen by an occupational therapist who discusses issues related to prevention of lymphedema. Women are not followed by either the physiotherapist or the occupational therapist after discharge from the hospital.

Women in the Usual Care group will not be given a home program of exercises, apart from those described in the pamphlet. To control for attention from the research assistant, they will meet with the research assistant fortnightly at which time their arm will be assessed with multifrequency bioimpedance analysis [15] for the development of lymphedema, but no specific advice will be given about exercise and management.

#### Exercise group

Commencing Week 4 following surgery, women will attend 8 weekly exercise sessions comprising stretching exercises and resistance training, and will commence a daily home program of similar exercises. We have used these exercises in our pilot study [10], and they are well tolerated.

Each week, there will be a supervised weekly session at which women will perform the shoulder exercises targeting the muscles and shoulder movements likely to be at risk. Stretches will consist of prolonged holds of at least 5 minutes duration. The stretches are performed in supine and are undertaken for the shoulder extensors, and for pectoralis major and minor muscles. For women unable to achieve >90 deg forward flexion, shoulder extension and abduction stretches will be performed whilst seated. For both stretches, the arm will be elevated in the appropriate direction and supported on pillows; the aim of these stretches is to provide a comfortable stretch in the region of the participant's axilla. Each of these stretches will also be held initially for 5 minutes and progressed up to 20 min. Once shoulder flexion >90 deg is achieved, the participant will undertake the stretches in supine. The muscles targeted for resistance training include the shoulder flexors, abductors, external rotators and horizontal flexors. For strength training, the resistance will be determined by the Borg Effort Scale [16] and provided by free weights. Each week, the exercises will be monitored, and progressed as required.

In addition to the weekly supervised sessions, women will perform a daily home program. The program will consist of i) a daily stretching program and ii) a strengthening program undertaken on alternate days. The stretching program will be the same as that undertaken at the weekly supervised session. For the strengthening program, the same muscles will be trained as in the weekly supervised sessions but rather than free weights, the resistance will be provided by theraband. Participants will be instructed to perform two sets of 8 – 12 repetitions for each exercise. Participants will be instructed to work at a target of 15 ('Hard') on the Borg Effort Scale [16]

At the conclusion of the program, women will be encouraged to continue the home program. A compliance diary will be provided to record the number of times each exercise was performed each day. In addition, women in both groups will be asked to record any other treatments that they have received the dose, and the effect.

### Measurement

All measurements will be undertaken by a research assistant blinded to the group to which women were allocated. Variables will be measured before randomization, at 8 weeks (the end of the intervention phase) and then at 6 months to determine the effect of the intervention on physical and psychosocial outcomes. In addition, information about the breast cancer treatment regimen, pathology report, age, weight, and previous shoulder pathology will be obtained from the patient's medical record at the baseline assessment. Occurrence of side-effects and adverse events will be evaluated at each measurement occasion.

The primary outcome measure for treatment efficacy is arm symptoms on the operated side, derived from 3 items of the Breast Module (BR23). The BR23 is a 23-item survey specific to women with breast cancer. The 3 selected items ask whether in the past week the woman has had pain in her arm or shoulder, a swollen arm or hand, and whether it was difficult to raise or move her arm sideways. For each question, there are 4 possible responses, ranging from 'not at all' to 'very much'. The raw scores for these questions are summed and then subjected to linear transformation to provide an overall score, with a maximum of 100. A high score indicates a high level of symptoms. The primary endpoint for the trial is change in primary outcome from baseline to 6 months.

Secondary outcomes include other aspects of quality of life and measures of physical impairment.

Quality of life will be measured using the European Organisation for Research and Treatment of Cancer Quality of Life Questionnaire Version 3 (QLQ-C30) and the Breast Module (BR23). These surveys are specific to cancer patients and comprise a global health status/quality of life scale, as well as functional and symptom scales. These questionnaires are reliable, valid and sensitive to change and able to distinguish patients in different disease stages and with different performance status [17-19].

Shoulder range of motion will be assessed using an inclinometer and a standardised protocol will be followed to minimise compensatory movements. Passive forward flexion, external rotation and horizontal abduction at the shoulder will be assessed in a supine position and with gravity as the standardised force. Active abduction will be assessed in the sitting position. Each arm will be measured separately. Pain at the end of the passive range of each movement will be measured using a standardised 10 cm visual analogue scale.

Maximal isometric shoulder strength will be measured objectively with a dynamometer using a standardised protocol. The arm will be positioned at 90 degrees elevation to assess forward flexion, abduction, and horizontal abduction and adduction. Movement in these planes has been selected as it has been shown to be weak following breast cancer surgery [20,21]. For each direction, women will perform 3 maximum voluntary contractions, and the highest of the three attempts will be recorded. Each arm will be measured separately.

The presence of lymphedema will be measured non-invasively using multiple frequency bio-impedance analysis. This analysis identifies early changes in tissue fluid accumulation [22] and is substantially more sensitive than total limb volume measurements in detecting changes in extracellular fluid volume. It has an extremely low (<1 %) false-positive rate for detecting lymphedema [22]. In addition, circumference measures at multiple sites on each arm will be obtained using a standardised measurement technique.

All women will be requested to record use of resources (number and type of health care contacts, medication use, adjunct treatments) during the trial period and the effect of these treatments.

The occurrence of lymphedema, regardless of treatment group allocation, is considered an 'adverse' event. If lymphedema develops, women will be referred to the Breast Cancer Nurse for referral to an appropriate specialist.

### Data analysis

#### Sample size calculations

We will recruit 180 women, 90 to each of the two treatment groups. This will give 80% power to detect as significant at the 2-sided 5% significance level a difference of 12 points (out of 100) for arm symptoms derived from the BR23, based on our pilot data standard deviation of 25. In addition, we have allowed for 20% mortality and loss to follow-up. Based on our pilot data, we will also be able to detect at least 10° difference in range of motion at the shoulder and 5 N difference in shoulder strength.

#### Statistical analysis

Treatment group will be coded to enable blinded analysis, which will be by "intention-to-treat". For the primary outcome measure, the change from baseline score for arm symptoms on the operated side derived from the BR23 will be determined. The mean change will be compared between the two groups using Student's two-sample t-test.

Our secondary analyses will examine the effect of adjusting for the stratifying factor (type of surgery) or any important prognostic factors that show a clinically important imbalance between groups. This will be done using multiple linear regression, with the baseline arm symptoms score as a covariate and the final arm symptoms score as the outcome variable.

For measures of strength, range of motion, and lymphedema, the difference between the operated and non-operated side will be determined. These differences at 6 months will be compared using a two-sample t-test or distribution-free equivalent, as appropriate. For other aspects of the quality of life score, the mean changes from baseline will be compared between the two groups using Student's two-sample t-test. As for the primary outcome, multiple regression analyses will be used for all secondary variables to adjust for covariates, including baseline differences.

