### Randomization

An investigator who has no direct contact with the subjects will be responsible for generating the randomisation list. Randomisation will be stratified by whether women receive axillary node resection or sentinel node biopsy. The randomisation list will be used to prepare numbered opaque envelopes with the group allocation sealed inside by a person not involved in the study. Immediately after baseline assessment, women will be randomly allocated to either the usual care or exercise group. The protocol for this study is registered with the Australian Clinical Trials Registry (ACTRN012606000050550).

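### The primary test is an unadjusted t-test on change, while the generally more precise model with baseline score and surgery stratum is only secondary

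*Protocol article*

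**What the plan says.** The Measurement section of the protocol article defines the primary endpoint as the change in BR23 arm symptoms between baseline and 6 months. Under Statistical analysis, the primary comparison is: "The mean change will be compared between the two groups", by Student's two-sample t-test. No covariate enters this test.

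Under Randomization: "Randomisation will be stratified by whether women receive axillary node resection or sentinel node biopsy". That factor returns only in the secondary analyses. These adjust for the stratifier or for prognostic factors that turn out to be imbalanced, by multiple linear regression "with the baseline arm symptoms score as a covariate and the final arm symptoms score as the outcome variable".

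Under Sample size calculations, 90 women per group, with a 20% allowance for death and loss, are said to give 80% power for "a difference of 12 points (out of 100) for arm symptoms derived from the BR23, based on our pilot data standard deviation of 25". The text does not say whether that SD belongs to a single score or to a change, and it gives no correlation between baseline and follow-up.

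**The concern.** Subtracting the baseline fixes its coefficient at 1. ANCOVA estimates the coefficient from the data, so in large samples its residual variance is never above that of the change score, and it is clearly lower when baseline predicts follow-up only moderately. A moderate correlation is plausible here: baseline is 4 weeks after surgery, some women go on to radiotherapy, chemotherapy or reconstruction, and the score rests on three four-level items.

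The stratifier raises a related point. If change in symptoms differs between axillary node resection and sentinel node biopsy, leaving the stratum out keeps that variation in the standard error, although the randomisation was built to balance it.

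At stake are the width of the primary confidence interval and, on one reading of the pilot SD, whether the planned test reaches the stated power. The article explicitly chooses the primary test and ranks the regression second, so this is not a detail left to a document that is not shown.

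**Working it through.** **Inputs from Sample size calculations:** two-sided 5% level, 80% power, difference 12, SD 25, 90 per arm, 20% loss. Evaluable women per arm: 90 × 0.8 = 72.

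**Input not in the document:** the correlation r between the baseline and 6-month scores. It is assumed to lie between 0.2 and 0.7.

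**Step 1: reproduce the plan's figure.** The normal approximation gives 2 × (25 × (1.960 + 0.842)/12)² = 68.1, so 69 per arm. The noncentral t gives 70 per arm, and 70/0.8 = 87.5, so 88 per arm against 90 planned. With 72 per arm, the noncentral t gives 81.6% power. The stated size therefore reproduces when 25 is the SD of the quantity being tested.

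**Step 2: information lost by the change score.** Let both time points have SD σ.

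- Variance of change: 2σ²(1 − r)
- ANCOVA residual variance: σ²(1 − r²)
- Ratio, ANCOVA to change: (1 − r²)/(2(1 − r)) = (1 + r)/2
- Information lost: 1 − (1 + r)/2 = (1 − r)/2

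This gives 40% at r = 0.2, 35% at 0.3, 25% at 0.5 and 15% at 0.7.

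**Step 3: unequal SDs.** Set the baseline variance to 1, let the 6-month SD be k, and take r = 0.6. The change variance is 1 + k² − 2rk and the ANCOVA residual variance is k²(1 − r²).

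- k = 1.5: 1 + 2.25 − 1.80 = 1.45 against 2.25 × 0.64 = 1.44. The loss is under 1%.
- k = 1: 0.80 against 0.64. The loss is 20%.
- k = 2/3: 1 + 0.444 − 0.800 = 0.644 against 0.444 × 0.64 = 0.284. The loss is about 56%.

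The direction is stable, but the size depends on figures that the document does not give.

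**Step 4: power if 25 is the SD of a single score** (72 per arm, difference 12, equal SDs, noncentral t). SD of change = 25√(2(1 − r)); ANCOVA residual SD = 25√(1 − r²).

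| r | SD of change | Power, t-test on change | ANCOVA SD | Power, ANCOVA |
|---|---|---|---|---|
| 0.2 | 31.6 | 62% | 24.5 | 83% |
| 0.3 | 29.6 | 68% | 23.8 | 85% |
| 0.4 | 27.4 | 74% | 22.9 | 88% |
| 0.5 | 25.0 | 82% | 21.7 | 91% |
| 0.6 | 22.4 | 89% | 20.0 | 95% |
| 0.7 | 19.4 | 96% | 17.9 | 98% |

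The t-test reaches 80% at r of about 0.48.

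**Step 5: power if 25 is already the SD of change.** The t-test has 82% power whatever r is. The ANCOVA residual SD is 25√((1 + r)/2), which gives 96% at r = 0.2, 91% at 0.5 and 87% at 0.7.

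**Step 6: the stratum.** The document gives no estimate of how change differs by type of axillary surgery, so any further gain from including the stratum cannot be calculated.

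**The case against.** The strongest reply is that nothing here is wrong in the sense of invalid. Under randomisation, the t-test on change is unbiased for the mean difference, it matches the endpoint as defined, and omitting a stratifier generally makes it conservative. Baseline is used, through the subtraction. The regression is already pre-specified, so the adjusted estimate will be produced in any case. All of this stands, and it makes the point one of efficiency.

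Two stronger readings are tempting. A reader might infer that the plan wastes 15% to 40% of its information as a matter of fact. The documents do not support that: the range needs an assumed r and equal SDs, and step 3 shows how far it can move. A reader might also infer that the stated 80% power hangs on an unstated correlation. That follows only if 25 is the SD of a single score. Because the endpoint is a change, the figure may well be the SD of change, and then the stated power holds at any r. A condensed article may also leave that detail to the full protocol, so its absence is not a fault in itself.

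The stratum argument is limited too. A difference between surgery types that stays constant over time cancels in the change score. The Discussion links arm morbidity to the type of axillary operation but says nothing about change from week 4 to 6 months.

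These points limit the size of the problem without removing it: the result labelled primary is still the one from the generally less precise analysis.

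**Conclusion.** The point holds as a loss of precision, not as bias or an invalid test. The article makes an unadjusted change-score t-test primary and ranks second a model that is at least as efficient in large samples. With equal SDs and r from 0.2 to 0.7, both assumptions, the loss from not modelling baseline is 40% to 15% of the information. Outside those assumptions it could be close to nil or larger.

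The sample size is arithmetically sound. On either reading of the pilot SD, and at every r examined with equal SDs, ANCOVA exceeds 80% power at 72 per arm. The planned t-test does so if 25 is the SD of change, or if it is a single-score SD and r is about 0.48 or more.

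A smaller weakness is that the secondary model adjusts for the stratifier or for factors found to be imbalanced. The wording does not guarantee that the stratum is included, and it lets the covariates depend on the observed data.

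**What to change.** Make the primary analysis a linear model of the 6-month arm symptoms score on treatment group, baseline arm symptoms score and type of axillary surgery (node resection or sentinel node biopsy). Include the stratum always, whatever the observed balance. Report the adjusted mean difference with its 95% confidence interval. Keep the t-test on change as a sensitivity analysis, and keep adjustment for other imbalanced prognostic factors as secondary.

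The endpoint need not be redefined: with the baseline score in the model, the treatment coefficient is the same whether the outcome is the 6-month score or the change. While the text is open, it would help to say whether the SD of 25 refers to a score or to a change.

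The cost is a sentence or two of wording, settled before the group codes are broken. No extra women, visits or data are needed.

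### Whether the operated arm is the dominant one is left out of the inter-limb comparisons of strength, range and lymphedema, which costs a little precision but causes no bias

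*Protocol article*

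**What the plan says.** Under Statistical analysis, the protocol article turns strength, range of motion and lymphedema into an inter-limb contrast: "the difference between the operated and non-operated side will be determined". The comparison stated first is unadjusted and uses the final visit only: "These differences at 6 months will be compared using a two-sample t-test or distribution-free equivalent, as appropriate".

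The same section then plans a second layer, in which "multiple regression analyses will be used for all secondary variables to adjust for covariates, including baseline differences". The covariates it describes, in the paragraph on the primary outcome, come from "adjusting for the stratifying factor (type of surgery) or any important prognostic factors that show a clinically important imbalance between groups".

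Under Measurement, the outcomes are taken at baseline as well: "Variables will be measured before randomization, at 8 weeks (the end of the intervention phase) and then at 6 months". Range and strength are measured on each arm. The background items are described thus: "information about the breast cancer treatment regimen, pathology report, age, weight, and previous shoulder pathology will be obtained from the patient's medical record". Randomisation is stratified by type of axillary surgery only, and women with bilateral operations are excluded. Hand or arm dominance appears nowhere in the article.

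**The concern.** Every woman has one operated arm, which is either her dominant arm or not. If the dominant arm is naturally stronger by some amount A, the operated-minus-non-operated difference moves up by A in women operated on the dominant side and down by A in the others, whatever the treatment does. In an unadjusted comparison that spread stays in the error term. A chance difference between groups in how often the dominant side was operated on also moves the two means apart.

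The provision for adjusting prognostic factors that look imbalanced cannot help with a factor that nobody recorded. What is at stake is precision for secondary outcomes that the Background section lists among the trial's aims (weakness, swelling and loss of range). The primary outcome, BR23 arm symptoms, is not an inter-limb difference and is unaffected.

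**Working it through.** **Inputs from the article (Sample size calculations).** 90 women per group, 20% loss, two-sided 5%, 80% power, 12 points with SD 25 for arm symptoms, and a detectable difference of 5 N for strength with no SD given.

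**The plan's own figure.** A t-test for 12 points with SD 25 needs 69.1, so 70 per group. Then 70/0.8 = 87.5, so 88 per group, close to the planned 90. Completers are 0.8 × 90 = 72 per group, which gives 81.6% power for 12 points. The sample size reproduces and is not affected by this point.

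**Implied strength SD (assumption: the 5 N is an inter-limb difference at 80% power with 72 per group).** By the normal formula, SD = 5 / [(1.96 + 0.842) × √(2/72)] = 5 / 0.467 = 10.7 N. The t-test version gives 10.64 N, so V = 10.64² = 113.1.

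**Dominance in the unadjusted test (assumptions: half the women are operated on the dominant side; A = 1 to 5 N).** A shift of +A or −A with probability one half has variance A². V is taken as already containing it.

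| A (N) | share of variance, A²/V | power for 5 N once removed (from 80%) |
|---|---|---|
| 1 | 0.9% | 80.3% |
| 2 | 3.5% | 81.4% |
| 3 | 8.0% | 83.2% |
| 4 | 14.1% | 85.6% |
| 5 | 22.1% | 88.8% |

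**Chance imbalance, unadjusted.** The SD of the between-group difference in the proportion operated on the dominant side is √(2 × 0.25/72) = 0.083. A 2-SD imbalance is 0.167, and it shifts the group difference by 2A × 0.167 = A/3: 1.0 N at A = 3 and 1.7 N at A = 5.

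**After the planned regression on the baseline inter-limb difference.** Let r be the correlation between baseline and 6 months within dominance groups (not given; taken as 0.3 to 0.7). The slope on baseline is b = [A² + r(V − A²)]/V, and the share of the dominance shift left over is 1 − b.

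- A = 3, r = 0.7: b = (9 + 0.7 × 104.1)/113.1 = 0.724. Left over 0.276, so the 2-SD shift is 0.276 × 1.0 = 0.3 N.
- A = 5, r = 0.3: b = (25 + 0.3 × 88.1)/113.1 = 0.455. Left over 0.545, so the 2-SD shift is 0.545 × 1.67 = 0.9 N.

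For A = 3 to 5 N, the share left over is 55% to 64% at r = 0.3, 39% to 46% at r = 0.5 and 23% to 28% at r = 0.7.

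**Extra power from adding dominance to that regression.** In a simulation with A = 4 N, 72 per group and 4,000 runs per setting, power moved as follows.

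| r | baseline only | baseline + dominance | gain (points) |
|---|---|---|---|
| 0.3 | 84.8% | 87.3% | 2.5 |
| 0.5 | 92.8% | 93.7% | 0.9 |
| 0.7 | 98.6% | 98.8% | 0.2 |

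Comparing residual variances V(1 − b²) and (V − A²)(1 − r²) directly gives gains of 2.3, 1.0 and 0.2 points, which agrees. In the simulation the gain was at most 0.6 points at A = 2 N and at most 3.3 points at A = 5 N.

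**The case against.** The strongest reply is that this is an argument from silence. The background list under Measurement covers items taken from the medical record, in an article that condenses a fuller protocol. An assessor could simply ask about handedness, and the full covariate list may sit in a document not shown. That stands: the article does not show that dominance goes unrecorded, and a reader should not infer it. What remains is the comparison the article does fix, an unadjusted 6-month test stated ahead of any adjusted one.

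Second, the plan already has a partial remedy. The baseline inter-limb difference carries the same dominance shift, so regressing on it removes part of the noise. This also stands, and it is why the figures for the unadjusted test must not be read as the net loss. How much is removed depends on the baseline-to-6-month correlation. The words on baseline differences could be read as between-group imbalances, but the parallel drawn with the primary outcome points to the baseline value as a covariate.

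Third, a reader might infer bias or a raised false-positive rate. Neither follows. Randomisation makes any imbalance in dominance random, and the standard error of the t-test already contains that variance. Nor is the 5 N claim undermined, since the implied SD is taken here to include dominance.

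Fourth, the dominance effect is assumed. At 1 to 2 N the gain is only 0.3 to 1.4 points even in the unadjusted test. This stands too.

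**Conclusion.** The point holds as a small, avoidable loss of precision in secondary outcomes. For strength, with an assumed advantage of 1 to 5 N and an implied SD of about 10.6 N, dominance takes about 1% to 22% of the variance in the unadjusted comparison, or roughly 0.3 to 9 power points. Once the planned baseline regression is used, adding dominance gains about 0.2 to 2.5 points at 4 N, and a 2-SD chance imbalance moves the estimate by about 0.3 to 0.9 N for 3 to 5 N.

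These figures rest on four assumptions that the article does not supply: the size of the advantage, an even split of operated sides, what the 5 N refers to, and correlations of 0.3 to 0.7. It would be tempting to extend the same size to range, bioimpedance and circumference. The article gives no basis for that, and nothing was calculated for them.

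**What to change.** Record hand dominance at baseline, if this is not already done. For strength, range and the inter-limb lymphedema measures, make the regression on the baseline inter-limb difference the main comparison, and include operated side dominant (yes/no) as a prespecified covariate whether or not the groups look imbalanced on it. Dominance is fixed before treatment, so adjusting for it is safe, and prespecifying it avoids a choice driven by the data.

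The cost is one question and one degree of freedom, with no change to sample size, randomisation or treatment. In the model above, most of the gain comes from moving to the baseline-adjusted analysis. The dominance term adds little if its effect is small or the baseline value is reliable.

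### Strength, range of motion and lymphedema: the main test uses 6-month side differences without baseline, which loses precision; for strength and range the side difference measures asymmetry, not the operated arm itself

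*Protocol article*

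**What the plan says.** All references are to the Protocol article.

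- **Outcome.** Statistical analysis: "For measures of strength, range of motion, and lymphedema, the difference between the operated and non-operated side will be determined".
- **Main test.** Same section: "These differences at 6 months will be compared using a two-sample t-test or distribution-free equivalent, as appropriate".
- **Adjusted analysis.** Same section: "As for the primary outcome, multiple regression analyses will be used for all secondary variables to adjust for covariates, including baseline differences". For the primary outcome, regression belongs to the secondary analyses; that paragraph begins "Our secondary analyses will examine the effect of adjusting for the stratifying factor (type of surgery" and goes on to prognostic factors that turn out imbalanced.
- **Comparison with other outcomes.** The primary outcome is tested as change from baseline, and so are the remaining questionnaire scales: "For other aspects of the quality of life score, the mean changes from baseline will be compared between the two groups".
- **Data available.** Under Measurement, variables are recorded before randomisation, at 8 weeks and at 6 months. For range and strength, "Each arm will be measured separately".
- **Intervention.** Exercise group: "The muscles targeted for resistance training include the shoulder flexors, abductors, external rotators and horizontal flexors". No side is named.
- **Detectable differences.** Sample size calculations gives 10° for range and "5 N difference in shoulder strength". It states no SD for either, and does not say whether they apply to the operated arm or to the side difference.

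**The concern.** There are two separate issues.

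1. **Baseline is left out of the main test.** Strength, range and lymphedema are the outcomes for which the article specifies a follow-up-only comparison; the questionnaire outcomes are compared as change from baseline. A baseline value of the same quantity is available for each woman, and randomisation was stratified by type of axillary surgery. A main test that uses neither gives up precision at no saving.

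2. **The outcome and the aim are not the same quantity.** The Background asks whether exercise prevents weakness and lost range in the upper limb. The planned outcome measures asymmetry between the arms. The two coincide only if the programme leaves the non-operated arm unchanged, and the description of the exercises does not settle that. The planned regression adds covariates but names no other outcome, so it does not change the quantity being estimated.

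**Working it through.** **Step 1. The stated sample size.** Inputs from Sample size calculations: difference 12, SD 25, two-sided 5%, 80% power, 20% loss, 90 per group.

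- Normal approximation: n = 2 × (1.960 + 0.842)² × 25² / 12² = 68.1, so 69 per group.
- t-test: 69.1, so 70 per group; 70 / 0.8 = 87.5, so 88 per group or 176 in total, consistent with 180 after rounding up.
- With 90 × 0.8 = 72 completers per group, power is 81.6%.

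The stated figure reproduces and is not in dispute.

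**Step 2. Implied SD for range and strength.** The article gives none. Assume 80% power with 72 per group for the stated differences. Then SD = d / (2.8016 × √(2/72)), and √(2/72) = 1/6.

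- 5 N: 5 / 0.4669 = 10.7 N
- 10°: 10 / 0.4669 = 21.4°

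**Step 3. Cost of omitting baseline.** Let ρ be the within-group correlation between the baseline and 6-month values of the same quantity. Adjustment multiplies the residual variance by 1 − ρ²; a change score multiplies it by 2(1 − ρ). Starting from 80% power for the unadjusted 6-month test (normal approximation):

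| ρ (assumed) | 1 − ρ² | Power, adjusted | Power, change score |
|---|---|---|---|
| 0.2 | 0.96 | 82% | 60% |
| 0.3 | 0.91 | 84% | 66% |
| 0.5 | 0.75 | 90% | 80% |
| 0.6 | 0.64 | 94% | 88% |
| 0.7 | 0.51 | 97.5% | 95% |

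Baseline falls only 4 weeks after surgery, so a low ρ is possible. Adjustment still gains at every ρ above zero, whereas a change score gains only above 0.5.

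**Step 4. What the side difference estimates.** Let Δ_O and Δ_N be the effects of allocation on the operated and non-operated arm. The between-group contrast in (operated − non-operated) is Δ_O − Δ_N. If Δ_N = f × Δ_O, it equals (1 − f) × Δ_O.

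For illustration, assume that 5 N is the operated-arm effect and that the side difference has the SD of 10.7 N from Step 2:

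| f (assumed) | Expected side difference | Power (normal) |
|---|---|---|
| 0 | 5 N | 80% |
| 0.10 | 4.5 N | 71% |
| 0.25 | 3.75 N | 56% |
| 0.50 | 2.5 N | 29% |

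The noncentral t gives 79.5% at f = 0 and 55.1% at f = 0.25. At f = 1 the expected difference is zero.

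**Step 5. Precision of the two outcomes.** With equal variances in the two arms and inter-arm correlation c, the side difference has 2(1 − c) times the variance of one arm: 1.0 at c = 0.5, 0.6 at 0.7 and 0.4 at 0.8. The operated-arm value adjusted for its own baseline has relative variance 1 − r², or 0.64 at r = 0.6.

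- Break-even without carry-over: 2(1 − c) = 0.64, so c = 0.68.
- At c = 0.8, the unadjusted side difference keeps the larger standardised effect until 1 − f = √0.40 / √0.64 = 0.79, that is, f of about 21%.

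Neither c nor r is given in the article.

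**The case against.** The case for the plan is substantial.

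- **Baseline.** Randomisation makes an unadjusted 6-month comparison unbiased, and a baseline-adjusted regression is planned for every secondary variable. This stands. What remains is which analysis is the main one, and the text gives that place to the unadjusted test.
- **Asymmetry is a legitimate outcome.** Surgery is one-sided, women with bilateral operations are excluded, and the other arm serves as each woman's own reference. The test validly estimates the effect on asymmetry. It removes variation between women and can be the more precise choice when the arms correlate strongly (Step 5). This also stands, and it rules out simply discarding the side difference.
- **Laterality is not stated.** A reader might infer that both arms are trained, so that the contrast is biased toward no effect. The article does not support that. It names muscles without a side, and its wording on the seated stretches refers to a single arm. A condensed article may leave this detail to the full protocol, and silence is not evidence of two-sided training.
- **The power figures in Step 4.** They apply an SD back-calculated from 5 N to the side difference while treating 5 N as the operated-arm effect. If 5 N already refers to the side difference, any carry-over is already netted out and the table does not apply.

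A reader might also think that a weak non-operated arm distorts the comparison. Weakness present before randomisation is balanced between groups in expectation, so it does not.

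**Conclusion.** The point holds in two limited parts.

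First, the main test for strength, range and lymphedema omits baseline and the stratifying factor. The consequence is lost precision, not bias. Under the 80% starting assumption, the power forgone runs from about 2 percentage points at ρ = 0.2 to 17.5 at ρ = 0.7.

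Second, the side difference answers a question about asymmetry, whereas the aim concerns function of the upper limb. The subtraction in Step 4 is exact, but whether it costs anything depends on an effect on the non-operated arm that the article neither states nor excludes. The fall from about 80% to about 55% power at 25% carry-over is therefore an illustration, not an estimate.

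The stronger conclusion, that the planned contrast is biased toward no effect and should be replaced, is not supported. These are secondary outcomes; the primary endpoint and the sample size of 180 are unaffected.

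**What to change.** 1. **Main analysis for strength, range and lymphedema.** Fit a linear model of the 6-month side difference with treatment, the baseline side difference and type of axillary surgery. Keep the unadjusted t-test or its distribution-free equivalent as supportive.
2. **Additional analysis for strength and range.** Report the 6-month operated-arm value from a linear model with treatment, the baseline values of both arms and type of axillary surgery. Read beside the side difference, it shows whether the other arm also responded.
3. **Clarify the text.** State whether the exercises involve one arm or both, and whether 10° and 5 N refer to the operated arm or to the side difference.

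The cost is a change of analysis wording; every value needed is already scheduled for collection. The downside is that the operated-arm analysis can be less precise than the side difference when the arms correlate strongly and the other arm does not respond. For that reason it is added rather than substituted.
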